### Outcomes {12}

The selection of outcome measures was based on the guidelines for clinical trials in patients with PSS by the European Research Network to Improve Diagnosis, Treatment and Health Care for Patients with Persistent Somatic Symptoms (EURONET-SOMA) [82]. Of main interest is the absolute change in scores in patient reported questionnaires from baseline (t0) to end of treatment (t1), the latter constituting the primary endpoint. The *primary outcome* will be self-reported somatic symptom severity, assessed using the revised version of the Screening for Somatoform Disorders (SOMS-7R [70, 71]) at baseline, during treatment (face-to-face sessions 1, 5, 10, and 15), post-treatment, and up to 6-month follow-up. Somatic symptom severity represents one of the core outcome domains in both research and clinical practice and is of high relevance to patients. It is considered as a continuous score and of primary interest is the absolute change from baseline (t0) to end of treatment (t1). The treatment differences will be displayed by a linear contrast for each study visit from the model with their 95% confidence intervals. The primary analysis population is the intention-to-treat (ITT) population consisting of all patients randomized. Long-term maintenance of the primary outcome, somatic symptom severity, will be evaluated using SOMS-7R scores at the 6-month follow-up. Additionally, we will qualify response and remission by change scores of the primary outcome (SOMS-7R) and remission by change in diagnostic status from baseline up to follow-up as categorical change parameters.

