
### Sample size {14}

Short-term CBT has demonstrated predominantly small to medium-sized between-group effects on somatic symptom severity in patients with medically unexplained physical symptoms or somatoform disorders (Standardized Mean Difference; *SMD* = 0.37; [18]) and medium- to large-sized within-group effects (*SMD* = 0.80; [83]), as corroborated by a multicenter CBT trial in outpatients with PSS (Cohen’s *d* = 0.70; [51]). Stand-alone internet-delivered CBT yielded small-sized average between-group effects on this outcome (*SMD* = 0.35; [84]) across chronic pain and functional somatic syndromes, whereas evidence from RCTs in individuals with diagnosed/probable SSD demonstrated medium- to large-sized effects (*d* = 0.68 to 0.91) [57, 85]. Evidence from depression research indicates small to medium-sized effects (*d* = 0.32 to 0.51) [34, 86] of added internet interventions to outpatient psychotherapy, which mirrors the treatment setting in the current study. Taken together, we expect the difference between our blended treatment and the enhanced treatment to be *d* = 0.40 for the primary endpoint. Thus, with a power of 80%, and a significance level of 0.05 (two-sided), 200 patients are required, when using a t-test. Because of some variability in effect sizes in the literature and the multicenter study introducing additional heterogeneity we planned the sample size conservatively by not using any correlation between measurements or between outcome and baseline variables. Based on treatment studies in this research field we expect a study drop-out for our primary endpoint (t1) up to 20% [51, 87], resulting in a sample size of *N* = 250 (125 per group). A study in the same setting concluded a similar sample size of 194 [51]. The calculation was performed with SAS 9.4.

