## Assignment of interventions: allocation

### Sequence generation {16a}

A randomization list is generated at Interdisciplinary Center for Clinical Trials (IZKS) at the University Medical Center Mainz by means of a validated SAS program (9.4 (SAS Institute, Cary, NC, USA)). The randomization ratio of the treatment group and the control group will be 1:1. Randomization will be stratified by study center. Block randomization with different block size will be applied.

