## Statistical methods

### Statistical methods for primary and secondary outcomes {20a}

The *primary endpoint* will be analyzed with a linear mixed-effect model (LMM) including center, use of prescribed psychopharmaceutic (ATC code N06A, yes/no), use of other (non-psychopharmaceutic) medications such as analgesics or antihypertensives (yes/no), mental disorder comorbidity (yes/no), intervention, time point, and the interaction term of intervention and time point as fixed effects, as well as baseline value as a covariate. An autoregressive covariance structure will be used as the primary covariance structure, given the ordered repeated measurements and the expected decrease in correlations over time. Robustness will be assessed using alternative covariance structures. The mixed-effects model uses all available observations and provides valid inference under the missing-at-random assumption. Model assumptions will be checked by residual plots and sensitivity to handling of missing data using multiple imputation. The test used is a linear contrast between the groups at post-treatment (time as categorical variable) and uses a *t*-statistic. Treatment differences will be displayed by adjusted mean differences and 95% confidence intervals. Follow-up data will be analyzed by the LMM approach taking a different contrast. The primary analysis will be performed with the ITT-population. For sensitivity additional subpopulations will be analyzed. Descriptive statistics will also be provided over time by treatment and in total. The primary parameter will also be displayed over time by a boxplot. For sensitivity also response and remission in the SOMS-7R are analyzed. Response will be operationalized as percentage improvement relative to the respective baseline score, (≥ 50% improvement within the pathological range of the SOMS-7R + 25% within the full range [93]). Remission will be coded if patients fulfill response criteria and transition from a dysfunctional to a functional score range in the SOMS-7R. As another remission criterion, we will analyze group differences in diagnostic status (SSD criteria fulfilled) at post-treatment and follow-up. Response and remission will be analyzed within a logistic regression model for each time point with the same covariates as the primary model. Descriptive statistics (absolute and relative frequencies) by time point will also be provided. Continuous secondary outcomes will be analyzed within an analysis model analogous to the primary analysis model and descriptive statistics will be given. Variables expected to have a skewed distribution like working disability days will be analyzed by Wilcoxon Rank Sum test. Categorical outcomes will be analyzed by Χ^2^-tests and will also be displayed by absolute and relative frequencies. Exploratively, health care utilization will be analyzed descriptively at the item level and compared between treatment groups. We will descriptively analyze the extent to which iSOMA is a normal part of the daily working routine of therapists’ post-treatment with the NoMAD. We will test group differences in the type and frequency of self-reported side effects in the NEQ with Χ^2^-tests and independent *t*-test for severity ratings. Potential moderators of the change processes between treatments include (a) demographics, (b) clinical characteristics (e.g., comorbidity, baseline symptom severity, traumatic experience via the CTS), as well as (c) treatment characteristics (e.g., parallel treatments, type of referral, preferences, treatment expectations via GEEE) at baseline. Mediators will be assessed at baseline, during treatment (sessions 1, 5, 10, 15), post-treatment, follow-up. We will examine the temporal, contemporaneous, and between-subject interaction of the therapists’ warmth and competence, treatment expectations, alliance, and psychotherapy outcomes with network models. To test the mechanisms of action of the blended therapy, mediating variables (self-efficacy, disability, and treatment agency) will be analyzed with structural equation modelling (SEM), assuming a lagged effect of a respective mediator on the primary outcome (dual simplex model [94]). This way, indirect effects via different pathways leading to the outcome can be examined. Model fit will be evaluated. Exploratory analyzes will examine further effect-modulating variables (e.g., treatment preferences, patient-, clinical, or treatment characteristics) as moderators (i.e., interaction effects with treatment group) or in the form of subpopulation/sensitivity analyzes (e.g., comorbidity status, treatment length, health care utilization) using the same LMMs as for the main analysis.

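### The primary autoregressive covariance is not said to allow visit-specific variances; in its homogeneous form the post-treatment standard error can be too small

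*Protocol article*

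**What the plan says.** Section {20a} of the protocol describes a linear mixed model with intervention, time point (categorical), their interaction, centre, two medication indicators, mental comorbidity and the baseline value. Baseline enters once; no baseline-by-time term is listed. On the covariance it says "An autoregressive covariance structure will be used as the primary covariance structure, given the ordered repeated measurements", and gives as a further reason that correlations should weaken as time passes. Other covariance structures are planned only as a robustness check. The confirmatory test is the group contrast at t1.

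Outcomes {12} places the primary outcome at baseline, "during treatment (face-to-face sessions 1, 5, 10, and 15), post-treatment, and up to 6-month follow-up". That makes six post-baseline visits. Intervention description {11a} gives roughly weekly sessions and at least six months of therapy, and the follow-up comes six months after that. Participant timeline {13} puts up to four probatory sessions, a medical check-up and randomisation after the baseline survey, so the gap from baseline to session 1 is several weeks but not fixed.

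The text does not say whether the structure is first order, homogeneous or heterogeneous in variance, or based on visit number or elapsed time.

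**The concern.** A homogeneous autoregressive structure gives every visit the same residual variance. The reason the protocol offers for its choice points the other way. If correlation falls with time, baseline predicts a score taken a few weeks later better than one taken half a year later. After baseline adjustment the residual variance is then small at session 1 and larger at t1, even when the raw SDs are equal. Pooling lends the precision of the early visits to the t1 contrast.

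At stake is the calibration of the trial's only confirmatory p-value and its confidence interval. The planned alternative structures would show a mismatch but would leave the primary p-value where it is.

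**Working it through.** **The plan's own figure.** Sample size {14} states "with a power of 80%, and a significance level of 0.05 (two-sided), 200 patients are required, when using a t-test", for an expected d of 0.40. Normal approximation: 2 × (1.960 + 0.842)² / 0.40² = 98.1, so 99 per arm. The exact t-test needs 100 per arm (power 80.4%), which is 200. With 20% drop-out, 200 / 0.80 = 250. The figure reproduces. It was obtained "by not using any correlation between measurements or between outcome and baseline variables", so it does not depend on the covariance structure.

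**Formula.** With complete data and a treatment effect at every visit, the model-based variance of the t1 contrast is proportional to the pooled variance, and the true variance is proportional to the residual variance at t1. In large samples:

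type I error = 2 × (1 − Φ(1.96 × √(pooled variance / t1 residual variance)))

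**Assumed inputs** (the protocol gives none): post-baseline visits at weeks 0, 5, 11, 17, 24 (t1) and 50; baseline 4 weeks before session 1; equal raw SDs of 1; correlation of scores d weeks apart = 0.4 + 0.5·exp(−d/12).

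1. Correlation with baseline at session 1 (d = 4): 0.4 + 0.5 × 0.717 = 0.758. Residual variance with its own slope: 1 − 0.758² = 0.43.
2. At t1 (d = 28): 0.4 + 0.5 × 0.097 = 0.448. Residual variance: 1 − 0.448² = 0.80.
3. With one common baseline slope (0.556 at the large-sample fit), the residual variances over the six visits are 0.47, 0.60, 0.71, 0.77, 0.81 and 0.86. The fitted pooled variance is 0.697, close to their simple mean of 0.70.
4. √(0.697 / 0.810) = 0.928, and 2 × (1 − Φ(1.96 × 0.928)) = 6.9%.

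**Sensitivity to decay and to the baseline gap** (same formula, equal SDs, complete data):

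| Assumed correlation | 4-week gap | 8-week gap | 12-week gap |
|---|---|---|---|
| 0.5 + 0.35·exp(−d/12) | 6.6% | 6.0% | 5.7% |
| 0.4 + 0.5·exp(−d/12) | 6.9% | 6.2% | 5.8% |
| 0.3 + 0.6·exp(−d/30) | 7.2% | 6.6% | 6.2% |

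**Other assumed settings, homogeneous form.**
- Stronger decay, equal SDs: standard error ratio 0.87-0.92, type I error 7.2-8.9%.
- SD rising 15-30% by t1: 8.6-11.0% with decaying correlation, 6.5-7.7% with constant correlation.
- Constant correlation 0.6, equal SDs: 5.0%.
- SD falling 15-30% by t1: 4.0-6.2% with decaying correlation, 1.9-3.4% with constant correlation.

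**Simulation under the null, N = 250.** With 3,000 trials per setting (Monte Carlo error about 0.4 points), the three settings in the table at the 4-week gap gave 6.0-8.1% with equal SDs. The second setting with the SD rising 15% gave 8.2-9.2%. An analysis of covariance at t1 alone gave 4.4-5.5%. A separate set of 2,000 runs per setting (error about 0.5 points), with other decay patterns, gave:

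| Model | Decaying correlation | Constant correlation |
|---|---|---|
| Homogeneous autoregressive | 7.9-9.4% | 5.3% |
| Time-based distance, one variance | 6.4-8.2% | 5.3% |
| Heterogeneous autoregressive | 5.4-6.1%; 6.9% in one setting | 5.2% |
| Analysis of covariance at t1 | 5.2-6.0% | 5.2% |

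The upper figures for the two pooled-variance models (9.4% and 8.2%) come from a setting in which the SD also rises 15%.

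**Which feature drives it.** Unequal spacing with equal residual variances makes the ratio 1, hence exactly 5.0% with complete data. A separate baseline slope per visit, with the pooled variance kept, changes the worked example to √(0.681 / 0.799) = 0.924, or 7.0%, no better than 6.9%. The pooled variance is the cause.

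**The case against.** The strongest objection is that the homogeneous form is an inference. A heterogeneous autoregressive structure fits the same words and stays close to 5% in most settings, and the exact variant is commonly left to the statistical analysis plan, which is not shown. This stands: the point is conditional, and leaving out the variant is not in itself charged as a fault. What remains is that the protocol positively names the primary structure and supports it with a rationale that, in the homogeneous form, works against the t1 standard error.

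Second, every correlation and SD above is assumed. This also stands. The baseline gap alone moves the result by about one point, and falling SDs can reverse the direction. A reader might infer that the confirmatory test is anti-conservative as written; the document does not support that.

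Third, a reader might blame the unequal visit spacing or the single baseline slope. The calculations show that neither is the main driver.

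Fourth, a reader might conclude that the statement "The mixed-effects model uses all available observations and provides valid inference under the missing-at-random assumption" is false. That property does presuppose an adequate covariance model, but no bias from drop-out was shown. In the first set of simulations the complete-data and drop-out rejection rates differ by at most 1.0 point, with Monte Carlo error of about 0.4 points on each.

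Finally, residual plots, alternative structures and multiple imputation are planned. The first two could reveal unequal variances, but none of them changes which p-value is primary.

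**Conclusion.** The concern holds in conditional form. If the autoregressive structure is homogeneous and correlations decay as the protocol expects, the t1 standard error can be too small. With equal SDs the type I error is then about 6-9%: near 6% with a long gap from baseline to session 1 or mild decay, near 9% with strong decay. Rising SDs make it worse, up to about 11% in the settings tried. Constant correlation with equal SDs gives 5.0%, and falling SDs can make the test conservative. All of this rests on assumed visit times, correlations and SDs. It justifies a recommended low-cost improvement, not a must-fix error.

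**What to change.** In section {20a} and in the statistical analysis plan:

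- Make an unstructured covariance over the six post-baseline visits the primary structure (6 × 7 / 2 = 21 parameters, N = 250), with Kenward-Roger degrees of freedom.
- Optionally add a baseline-by-time term. It does not cure pooling by itself, but the 6.9% setting for the heterogeneous autoregressive model suggests that the single slope can still matter under drop-out.
- Pre-specify the order if the model does not converge: heterogeneous Toeplitz, then heterogeneous autoregressive, both with robust standard errors.
- Keep the autoregressive model as a sensitivity analysis, with its exact form stated.

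The unstructured model itself was not simulated. The closest evidence is the analysis of covariance at t1, which likewise estimates the t1 variance on its own.

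The cost is wording, a possibly slightly wider confidence interval and a small convergence risk that the fallback covers. No new data are needed and the sample size stays at 250. Recruitment is planned to August 2027 and analysts stay blinded until database lock, so the change can be made without knowledge of results.

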
### Objectives {7}

The primary objective of this trial is to investigate the efficacy, that is to show that an integrated form of blended psychotherapy (iSOMA+) reduces somatic symptom severity significantly stronger than CBT enhanced with bibliotherapy (CBT+) from baseline to post-treatment.

Furthermore, we expect that iSOMA+, compared to CBT+, will lead to significantly greater reductions in secondary outcomes, including somatic symptom severity, adverse consequences of somatic symptoms, depression, anxiety, health anxiety and disability as well as significantly greater improvements in self-efficacy, somatic symptom coping, quality of life and experience in personal social systems from baseline to post-treatment and from baseline to the 6-month follow-up.

Thirdly, we expect that iSOMA+, compared to CBT+, will lead to a significantly higher rate of meaningful clinical change (response, remission) in somatic symptom severity.

Fourthly, we will investigate mechanisms of action, since previous trials have identified that motivational (e.g., self-efficacy, treatment agency) and functional (e.g., pain-related disability) characteristics are positively associated with treatment outcomes and may act as mediators of therapeutic change [39–41]. However, their role in blended psychotherapy is unclear. Therefore, we test whether an increase in self-efficacy, treatment agency, and a reduction in functional impairment will mediate the treatment effect of iSOMA+ compared with CBT+.

Exploratively, we will investigate to what extent (a) demographic characteristics of patients (e.g., gender), (b) clinical characteristics (e.g., baseline severity of somatic symptom distress, comorbidity), and (c) treatment-related factors (e.g., concurrent treatments, treatment expectations) moderate the treatment effect between the two treatment conditions (iSOMA+ vs. CBT+).

Furthermore, we will examine whether iSOMA+ differs from CBT+ with respect to changes in health care utilization from baseline to the end of treatment and from baseline to the 6-month follow-up. Treatment satisfaction and implementability will be tested. Finally, patient safety will be investigated, and no significant differences are expected in the type or frequency of serious adverse events (SAEs) and other side-effects between iSOMA+ and CBT+.

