### Trial design {8}

This is a prospective, multicenter, two-armed, active-controlled, parallel group, randomized controlled superiority trial that will be conducted at eight university outpatient psychotherapy centers in Germany. A total of 250 adult patients with SSD will be included, 125 patients per study arm. Participants will be randomly allocated to the two conditions. Both study groups receive 20 sessions of CBT. Additionally, the intervention group receives the iSOMA internet intervention, while the active control group receives a self-help booklet. Primary and secondary outcomes will be measured before randomization (baseline), during the course of treatment, after completion of the face-to-face treatment (post-assessment), and 6 months after end of treatment (follow-up) (see Fig. 1).

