### Methods in analysis to handle protocol non-adherence and any statistical methods to handle missing data {20c}

The primary analysis model is able to deal with missing at random data. Multiple imputation will be used as a sensitivity analysis. One hundred imputed datasets will be generated using fully conditional specification (chained equations). The imputation model will include variables from the primary analysis model as well as baseline, clinical, and outcome-related variables considered relevant for predicting missingness and/or outcome values. Each imputed dataset will be analyzed using the primary analysis model, and results will be combined according to Rubin’s rules. Further details regarding the imputation model will be prespecified in the statistical analysis plan.

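### The per-time-point logistic models for response and remission sit outside the planned multiple imputation, so as written they omit patients not assessed at that visit and ignore their in-treatment SOMS-7R scores

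*Protocol article*

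**What the plan says.** All references are to the protocol article.

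- **Objectives {7}** sets out, as a third expectation, that iSOMA+ "will lead to a significantly higher rate of meaningful clinical change (response, remission) in somatic symptom severity".
- **Outcomes {12}** defines the endpoints: "Additionally, we will qualify response and remission by change scores of the primary outcome (SOMS-7R) and remission by change in diagnostic status". The SOMS-7R is collected at baseline, sessions 1, 5, 10 and 15, post-treatment and follow-up. The diagnostic interview is not repeated during treatment.
- **Statistical methods {20a}** gives the model: "Response and remission will be analyzed within a logistic regression model for each time point with the same covariates as the primary model". The same section introduces the SOMS-7R versions of response and remission as sensitivity analyses. It claims validity under missing at random for the mixed model.
- **Missing data {20c}** plans 100 datasets imputed by chained equations and says what is done with them: "Each imputed dataset will be analyzed using the primary analysis model, and results will be combined according to Rubin’s rules". It leaves further detail of the imputation model to the statistical analysis plan.
- **Sample size {14}** expects the loss: "we expect a study drop-out for our primary endpoint (t1) up to 20" per cent. **Trial design {8}** gives the base: "A total of 250 adult patients with SSD will be included, 125 patients per study arm".
- **Criteria for discontinuing {11b}** invites patients who stop treatment to both later assessments.

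**The concern.** Response and SOMS-7R remission are computed from the same questionnaire as the primary outcome, but the two analyses treat an absent post-treatment score differently. The mixed model keeps a patient who has only session scores and lets those scores inform the estimate. A logistic regression at a single time point takes one outcome per patient, so a patient without that outcome contributes nothing. The section that could bridge this gap names only the primary model as the user of the imputed data.

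Two things are at stake. Information already collected is thrown away. Also, if the responder result and the mixed-model result disagree, nobody can tell whether dichotomising the score or the change in patient set and missing-data assumption is responsible. That weakens an analysis meant to show robustness.

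**Working it through.** **Step 1. The plan's own figures.** Sample size {14} gives "with a power of 80%, and a significance level of 0.05 (two-sided), 200 patients are required, when using a t-test", with an effect size of "0.40 for the primary endpoint". A two-sample t-test with 100 per arm has power 80.4%, so 200 is reproduced. Inflating for drop-out: 200 / (1 − 0.20) = 250. The number without a post-treatment score at the planning ceiling is 0.20 × 250 = 50, which leaves about 200 in the logistic model if nothing is imputed.

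**Step 2. Rate arithmetic.** The document gives no response rates, so true rates of 30% (CBT+) and 45% (iSOMA+) are assumed, a difference of 15.0 points. With drop-out proportion m:

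observed rate = (true rate − m × rate among the missing) / (1 − m)

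With m = 0.20 in each arm:

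- Missing patients respond like the observed in both arms: 0.45 − 0.30 = 0.150. No bias.
- Missing CBT+ patients respond half as often: (0.30 − 0.20 × 0.15) / 0.80 = 0.3375. Difference 0.45 − 0.3375 = 0.1125, or −3.75 points of bias.
- Missing iSOMA+ patients respond half as often: (0.45 − 0.20 × 0.225) / 0.80 = 0.50625. Difference 0.50625 − 0.30 = 0.20625, or +5.6 points of bias.
- Halved in both arms: 0.50625 − 0.3375 = 0.16875, or +1.9 points (odds ratio 2.01 against 1.91). With no true effect (30% in both arms) the bias is zero.

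Unequal loss also counts as an arm difference. With 15% loss in CBT+, 25% in iSOMA+, no true effect and response halved among the missing in both arms, the observed difference is 0.350 − 0.326 = +0.024.

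Scoring the missing as non-responders is not a neutral default. With random 20% loss in each arm it gives 0.80 × 0.150 = 0.120.

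**Step 3. Simulation using the interim scores.** Taken from Sample size {14}: d = 0.40, a within-arm change of 0.70 SD, and 20% drop-out. Taken from the trial design: N = 250. Assumed: correlation 0.8 between adjacent visits, baseline mean 2.5 SD above zero, response simplified to a fall of at least 25%, and drop-out driven by interim non-improvement through a logistic hazard. The slope is 0 in both arms (random), 0.8 in both arms (equal dependence), or 1.2 in one arm and 0 in the other. Ranges are over repeated runs.

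| Drop-out mechanism | True difference (points) | Observed-case difference (points) |
|---|---|---|
| Random in both arms | 0 or about 14.8 | essentially unbiased |
| Equal dependence, no effect | 0 | 0.1 |
| Equal dependence, d = 0.40 | about 14.8 | 14.3 to 14.5 |
| iSOMA+ only, no effect | 0 | +4.6 to +5.4 |
| CBT+ only, no effect | 0 | −5.0 |
| iSOMA+ only, d = 0.40 | about 14.8 | 19.2 to 20.0 |
| CBT+ only, d = 0.40 | about 14.8 | 9.6 to 10.1 |

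A moderate difference in dependence between the arms gave about 2 points. Response derived from imputed scores was unbiased in every scenario run. Scoring the missing as non-responders gave 7.7 to 16.3 points where the truth was about 14.8.

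**Step 4. Precision.** The SD of the log odds ratio was about 0.29 to 0.33 for observed cases and 0.26 to 0.30 for imputation-derived response, smaller with imputation in every scenario run. With random drop-out one run gave 0.31 against 0.29, a variance ratio of (0.31 / 0.29)² = 1.14. As a ceiling on what could be recovered, a simple comparison of 30% with 45% has power 69% with 125 per arm and 59% with 100 per arm. Imputation regains part of that gap, not all of it.

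**The case against.** The strongest answer is that this is a condensed article whose analysis plan is not shown, and that handling of missing supportive binary outcomes usually belongs there. That stands in part: the lack of a scoring rule for missing responders is not by itself an error here. It does not dispose of the point. The article defers the details of the imputation model, but it does say which analysis receives the imputed data, and it names only the primary model. An analysis plan that followed this text would leave the responder models on observed cases. An analysis plan may of course extend the imputation.

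A reader might infer that the protocol excludes patients with missing data, or that it tests the third objective on treatment completers. It says neither. Omission is what a single-time-point logistic regression does when nothing is imputed, and discontinuers are invited to the later assessments, so the analysed set is those assessed rather than those who completed treatment. The 20% is also a ceiling.

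A reader might further infer that the responder comparison will be biased. The documents do not support that. The biased results of about 5 points need dependence in one arm and none in the other. An arm difference is conceivable, because patients are unblinded and only iSOMA+ sends automatic reminders, but nothing in the documents shows it. Observed-case logistic regression is valid if missingness depends only on arm and the modelled covariates, and the planned covariates (center, medication, comorbidity) may absorb some of the dependence. The simulated response rule is simpler than the protocol's.

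Finally, these endpoints are secondary in weight. The analysis section labels the SOMS-7R versions as sensitivity analyses, although the objectives state a directional expectation for them.

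**Conclusion.** The point holds as an inexpensive improvement, not as a threat to the trial's main conclusion. As written, the responder analyses omit up to 50 of 250 randomised patients at post-treatment and make no use of their session scores. The firm consequence is lost precision, seen in every scenario simulated. Bias is conditional: about 5 response points in either direction under strong one-arm dependence, about 2 under a moderate arm difference, and negligible in the simulation under random or equal dependence. These sizes rest on the assumed correlation, baseline level, simplified response rule and drop-out slopes. The primary contrast, its missing-at-random handling and N = 250 are untouched. Loss at follow-up is not stated, so no size is given for that time point.

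**What to change.** Extend Missing data {20c} with a statement along these lines: SOMS-7R response and remission are derived for every randomised patient in each of the 100 imputed datasets; the imputation model includes arm and the SOMS-7R at all visits; the logistic model already stated in {20a} is fitted in each dataset and pooled by Rubin's rules. Report observed-case results and results with missing scored as non-response as sensitivity analyses.

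The cost is a few sentences and some programming. No new data are needed and the imputed datasets are already planned. Recruitment is planned to run until August 2027, so the change can be fixed before the analysts are unblinded. The downside is that the responder result then depends on the imputation model.

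Imputing SSD diagnostic status is optional and not part of this recommendation, because no interview is held during treatment to inform it.
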